### Secondary Outcomes

#### Self-Efficacy/ Expected Outcomes/ Planning

There will be a second questionnaire that will cover a range of psychological determinants. The pre-actional and maintenance self-efficacy, expected outcomes, and planning measures were adapted from Renner & Schwarzer's (2007) and Schwarzer's (2008) publication on assessment of the Health Action Process Approach Model (HAPA) and from Sienhotta et al.'s (2005) paper on physical activity.

#### Intentions

A measure of intention to saturated fat intake was adapted from Prestwich et al.'s study (in press) ('Over the next two weeks I intend to reduce my saturated fat intake'). A more detailed list of intentions was designed and tested with subjects for their external validity. The purpose has been to measure a number of saturated fat intake behaviours and add them up to get a total score of saturated fat intake. At follow-up, there were two further questions on participants' intentions to assess their cholesterol and blood pressure over the next month.

### Reactions to the Intervention

Subjects' opinions of the intervention were adapted from Bourdeaudhuij & Brug (2000), and Brug et al (1998). Two extra items were included on emotional reactions to the information presented ('I felt that the information.....was worrying', ... 'a wake-up call').

Table 2 below shows the questionnaires to be filled out at the three different study times.

Table 2. Study Assessments at the three different study times

| TIME 1                     | TIME 2                                                      | TIME 3                                                      |
|----------------------------|-------------------------------------------------------------|-------------------------------------------------------------|
| Intentions (saturated fat) | Intentions (saturated fat)                                  | x                                                           |
| x                          | x                                                           | Intentions (BP/cholesterol)                                 |
| Outcome Expectancies       | Outcome Expectancies                                        | x                                                           |
| Action SE                  | Action SE                                                   | x                                                           |
| x                          | Maintenance SE                                              | Maintenance SE                                              |
| Risk Perceptions           | Risk Perceptions                                            | x                                                           |
| FFQ                        | x                                                           | FFQ                                                         |
| x                          | x                                                           | Planning                                                    |
| x                          | Beliefs on Info received
(wake-up call, credibility etc) | Beliefs on Info received
(wake-up call, credibility etc) |

### 5.3 Study Duration

This study requires three online visits to a web site. The same subjects will not be contacted in the future to fill out any other information on these risk tools. The whole process, including screening and main study phase, should not last more than 3hours.

### 5.4 Dispensing and Accountability of Study Supplies

N/A

### 5.4 Continuation of Treatment

The subjects will not have access to the Heart-Age after completion of the study. The current link will be only designed to be used during the study.

## 6. Premature Withdrawal

### 6.1 Withdrawal from the Study

If a subject meets the inclusion criteria but decides to withdraw mid-way through the study then no data will be uploaded in the system and a request will be made to virtual surveys for this person to be replaced by another subject with the same characteristics.

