#### **1.4 Brief Description of Intervention**

The primary aim of the current study is to assess Heart-Age's motivational properties and its combined effects when used with planning on subjects' saturated fat intake.

Four sets of subjects will enter the online study site at three different times. In specific at **Time 1**, subjects will be invited to participate in the study by an online recruitment agency, which will also carry out the screening process. Once, subjects have been accepted in the study they will be asked to fill out three questionnaires: a) a self-reported dietary intake questionnaire, b) a self-reported questionnaire on various social-cognitive variables. At **Time 2**, which will be a week later, subjects will be randomly allocated into one of four conditions. In the most advanced condition subjects will go through the Heart-Age tool and then they will be asked to form a concrete plan on how to reduce saturated fat intake over the next two weeks. In the second and third conditions, subjects will be presented either with the Heart-Age tool or a planning session. There will be a control group, who will fill out questionnaires at pre-study, main study phase and post-study. At **Time 3**, subjects will be invited to fill-out again the same dietary measures of food intake and the questionnaire on the social-cognitive determinants. Study subjects will be rewarded for their participation in the study at Time 1 and 3 and will enter a prize draw of £200 in Amazon vouchers. This will be upon completion of study phase 3.

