## 4. Study Population

### 4.1 Total Number and Nature of Subjects

We will over-recruit at Time 1 to be able to take into account any drop-outs likely to occur over the study period. The aim will be to end up with 400 (or more) participants at Time 3. 100 subjects will be used for each cell of a 2x2 factorial design with the factors 'use of the Heart-Age tool' and 'use of planning'. Thus 200 subjects will use the Heart-Age site, 100 of these will plan how to reduce their saturated fat intake and the other 100 will not. Of the remaining 200 subjects, 100 will also be asked to plan how to reduce their saturated fat intake. The final 100 will act as a Control group (neither using the Heart-Age tool nor planning how to reduce their saturated fat intake).

Subjects will be recruited from both genders, be 30-60 years old and will have a high level of at least one risk factor for CHD (normally obesity). This inclusion of subjects with at least one risk factor has been deliberate. It is believed that these subjects,

though at no immediate risk of developing heart disease, will be more likely to benefit from presentation of information on their heart-health. If the information is motivating enough then they will hopefully decide to take some action to maintain or improve their future heart-health. Obese and overweight people are also expected to take into consideration their weight when making health-related judgements. Thus they should consider themselves as being at higher risk than people of average weight (Renner et al, 2000).

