### 6.2 Consequences of Missing Assessments

There are three assessment points in this study. Virtual Survey has suggested a 2/3 drop out from one study phase into the next. To account for this, 900 subjects will be recruited to end up with 400 at the end of the study.

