### **9.4. Data Protection**

Information relating to this study will be kept confidential and the subjects' right to check personal data will be fully protected in accordance with the Data Protection Act 1998. Use of Case Record Forms is not applicable in this study since all information will be gathered via an online system. Each subject will be allocated with a unique ID at the recruitment stage (by Virtual Surveys) which will remain the same until the end of the study. Subjects will be responsible for entering their data on the system and no personal details such as (first name, last name and email addresses will be asked of the subjects). However, subjects will be required to fill out personal health information, gender, date of birth into the website in order to receive feedback at the end of the study.

The subject may choose not to provide certain information, but this may mean they will not be able to complete the study and their data will be replaced by new

participant data. The site will not contact the user and Unilever Corporate Research will not knowingly sell, rent, or trade the personal information collected.

All web-based interaction data will be stored for a period of five years in a secure central database hosted by Tessella Services on behalf of Unilever. Data files on the mainframe will be backed-up automatically. All data files will be backed-up and stored in a secure location.

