### **3.5 Final report**

A summary will be issued within four weeks of study completion and a final report within 4 weeks of sponsor's comments. This report should include number of subjects enrolled, number of subjects dropped/withdrawn, adverse events, deviations, amendments, statistical analysis and general or specific comments from the investigator. Additionally, the contract laboratory will provide the sponsor/study coordinator with the electronic data.

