**Redirect: SSI thank you page (no payment)**

**QUOTAS (PER COUNTRY) / ASSIGN TO CELL:**

| HA+Planning              |                 | Heart-Age              |                 | Planning               |                 | Control Group          |                 |
|--------------------------|-----------------|------------------------|-----------------|------------------------|-----------------|------------------------|-----------------|
| Age                      | Gender          | Age                    | Gender          | Age                    | Gender          | Age                    | Gender          |
| 30-45
years
(N=50) | Males
(25)   | 30-45
years
(50) | Males
(25)   | 30-45
years
(50) | Males
(25)   | 30-45
years
(50) | Males
(25)   |
|                          | Females
(25) |                        | Females
(25) |                        | Females
(25) |                        | Females
(25) |
| 45-60
years
(N=50) | Males
(25)   | 45-60
years
(50) | Males
(25)   | 45-60
years
(50) | Males
(25)   | 45-60
years
(50) | Males (25)      |
|                          | Females
(25) |                        | Females
(25) |                        | Females
(25) |                        | Females
(25) |

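### Section 6.1 withholds the data of subjects who withdraw and replaces them; applied after allocation at Time 2, this stops the comparison being one of the groups as randomised

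*Protocol*

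**What the plan says.** - **Withdrawal (section 6.1).** For an eligible subject who decides to leave part-way, "no data will be uploaded in the system and a request will be made to virtual surveys for this person to be replaced" by another person with matching characteristics. The section does not separate withdrawal before allocation from withdrawal after it. It does not say whether the replacement is randomised afresh or put in the vacated arm.
- **Withheld information (section 9.4).** A subject may decline to give certain information, but "this may mean they will not be able to complete the study and their data will be replaced by new" participant data.
- **Allocation (section 1.4).** This is at Time 2, "which will be a week later, subjects will be randomly allocated into one of four conditions". The study schematic and section 5.1 also place it in Phase 2.
- **Outcome (sections 5.2 and 11.1).** The food frequency questionnaire is taken at Times 1 and 3, and the primary endpoint is the change from baseline to study completion.
- **Expected attrition (sections 4.1 and 6.2).** "The aim will be to end up with 400 (or more) participants at Time 3"; to allow for drop-out, "900 subjects will be recruited to end up with 400 at the end of the study".
- **Reporting (Part III, section 3.5).** The final report must give the "number of subjects dropped/withdrawn".

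**The concern.** A randomised comparison is protected because the groups were formed by chance and everyone allocated stays in view. Section 6.1 gives that up for any subject who withdraws after Time 2. The Time 1 questionnaire and Time 2 measures are never captured, and the place goes to a person selected because someone else left.

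Matching on recorded characteristics does not match on motivation or dietary response. If the replacement is put straight into the vacated arm, that person's arm is set by who left and not by chance. If the replacement is randomised afresh, the new allocation is sound, but the withdrawn subject is still erased.

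Loss could plausibly differ by arm. The arms receive a risk score, a planning task, both, or questionnaires only. Time 2 length depends on the condition, and section 1.5 names worry about the Heart-Age score as the one potential risk. If loss also depends on whether the subject cut saturated fat, the completers can show a difference that the interventions did not cause.

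**Working it through.** **1. How many allocated subjects could lack the outcome.** Inputs: 900 recruited, 400 at the end, two transitions (section 6.2), allocation at Time 2 (section 1.4).

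- Section 6.2 says "Virtual Survey has suggested a 2/3 drop out from one study phase into the next". Read literally: 900 × 1/3 = 300, then 300 × 1/3 = 100. This does not give 400.
- Read as two-thirds retained: 900 × 2/3 = 600, then 600 × 2/3 = 400. This reproduces the protocol's figure.
- On that reading, loss after allocation is (600 − 400)/600 = 200/600 = 33.3%. The 600 is inferred; the protocol does not print it.
- Other readings give more: the literal drop-out gives 200/300 = 66.7%. If arms were assigned at screening, as the Appendix 6 line "QUOTAS (PER COUNTRY) / ASSIGN TO CELL" could suggest, it is 500/900 = 55.6%.

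These figures cover loss of every kind. The share that is active withdrawal under section 6.1 is not stated and cannot be derived.

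**2. Illustration of the bias.** Let p be the true proportion reducing intake, the same in both groups, so there is no true effect. Let dr and dn be the drop-out rates among reducers and non-reducers. Among completers:

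observed proportion = p(1 − dr) / [p(1 − dr) + (1 − p)(1 − dn)]

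p = 0.10 is the lower proportion in section 11.3. The drop-out rates are assumptions, with dr = 0.20 in both groups.

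| dn | Calculation | Observed |
|---|---|---|
| 0.45 | 0.080 / (0.080 + 0.495) = 0.080 / 0.575 | 13.9% |
| 0.25 | 0.080 / (0.080 + 0.675) = 0.080 / 0.755 | 10.6% |
| 0.40 | 0.080 / (0.080 + 0.540) = 0.080 / 0.620 | 12.9% |
| 0.30 | 0.080 / (0.080 + 0.630) = 0.080 / 0.710 | 11.3% |

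- dn 45% v 25%: false difference of about 3.3 points.
- dn 40% v 30%: about 1.6 points.
- Design difference for the factor comparison (section 11.3): 8 points.
- Overall loss in the first case is 1 − 0.575 = 42.5% and 1 − 0.755 = 24.5%, averaging 33.5%, close to the one-third in step 1.

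**3. What can still be done without the withdrawn data.** The planned comparison is of a binary outcome, reduced or not. Given only the numbers allocated per arm, missing subjects can be counted as not reduced. In this illustration that gives 0.10 × 0.80 = 8% in both groups and no false difference, but only because reducers are lost equally in both.

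Extreme bounds are also possible. With 300 per factor level, 200 observed, and 10% v 18% reducing (20 and 36 subjects), the difference lies between 36/300 − 120/300 = −0.28 and 136/300 − 20/300 = +0.39. Bounds this wide say little, which is why the baseline and Time 2 data are worth keeping.

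**The case against.** The strongest reply is that section 6.1 concerns people who decide to withdraw, while ordinary attrition is handled in section 6.2 by recruiting 900. The Appendix 6 invitation closes the project at 900, which also sits badly with replacing every lost subject. Replacement between Time 1 and Time 2 happens before allocation and does no harm to randomisation. Matching characteristics may mean no more than the age and gender quota. All of this stands, and it limits the point to withdrawal after allocation.

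Four stronger readings are tempting, and the documents do not support them:

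- **That the rule discards all of the roughly 200 subjects lost after allocation.** Section 6.1 does not cover silent non-return.
- **That no sensitivity analysis would be possible.** Step 3 of the working shows two that need only the numbers allocated.
- **That the final report could not meet its own requirement.** Part III, section 3.5 asks for a count. The recruitment agency issues IDs, keeps an enrolment log and holds the screening answers, and nothing says these are deleted.
- **That the bias would equal the whole design effect.** With half of subjects reducing, the same drop-out rates give 0.400/0.675 = 59.3% v 0.400/0.775 = 51.6%, or 7.6 points. But the 8-point design difference is set at a 10% rate, where the figure is 3.3.

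The analysis set and imputation method may properly be left to the analysis plan announced in section 11.2. That does not answer this point, because section 6.1 is a rule about capturing data.

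**Conclusion.** The point holds for subjects who withdraw after allocation at Time 2. For them, section 6.1 as written removes randomised subjects' data and substitutes people selected afterwards. Section 9.4 does much the same for those who cannot complete because they withhold information.

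The number affected is unknown. The one-third figure is total loss after allocation, and it rests on reading section 6.2 as two-thirds retained and on allocation at Time 2. The bias of about 3.3 points (1.6 in the milder case) rests on assumed drop-out rates. It describes completer analyses generally and does not predict the effect of section 6.1 alone. Keeping the data would not remove such bias, but it would allow the bias to be examined and partly adjusted for. The rule needs settling before recruitment.

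**What to change.** Amend section 6.1 and the matching sentence in section 9.4 as follows:

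1. Keep all data entered up to withdrawal, unless the subject asks for deletion.
2. Allow replacement only before allocation at Time 2, since recruiting 900 already covers later losses. Align the cell-assignment line in Appendix 6 with that timing.
3. Keep every allocated subject in the allocated arm, and state that this applies to withdrawal and to non-return alike.
4. Report loss after allocation by arm.
5. Add a sensitivity analysis that counts subjects with missing Time 3 data as not reduced. Further handling of missing data can go in the analysis plan.

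The cost is protocol wording, a change to how partial entries are captured, and some analysis work. No additional subjects are required.

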### 6.2 Consequences of Missing Assessments

There are three assessment points in this study. Virtual Survey has suggested a 2/3 drop out from one study phase into the next. To account for this, 900 subjects will be recruited to end up with 400 at the end of the study.

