## **APPENDIX 6 – Recruitment Agency Screening**

### **Health Check Survey: Draft Questionnaire v2 2010 – Email Invite**

**Invite :**

From [name]  
Subject: Help us with our research

---

Dear panel member,

Today, we are inviting you to take part in a Health Check survey focusing on heart-health and healthy eating, which will involve carrying out a number of tasks. This will involve interacting with the system at three different times. The first time will not take more than 30 minutes. All those eligible and completing all three different interactions will be paid <<pointsAsMoney>> and their name will be also entered into a prize draw.

Instructions on how to take part can be found below. We look forward to hearing your opinions.

You can participate with this research project until <<end\_date>>. Please note this research project is limited to 900 respondents. Once 900 suitable respondents have completed the survey the project will be closed.

[name]  
SSI

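### Section 6.2 states a 2/3 drop-out per phase, but 900 recruits leave 400 only if 2/3 are retained; the screener's 400-place quota grid also conflicts with an intake of 900

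*Protocol*

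**What the plan says.** Section 6.2 of the protocol sets out the attrition allowance. It notes that "There are three assessment points in this study", reports that "Virtual Survey has suggested a 2/3 drop out from one study phase into the next", and concludes that "900 subjects will be recruited to end up with 400 at the end of the study".

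Section 4.1 gives the intent: "We will over-recruit at Time 1 to be able to take into account any drop-outs likely to occur over the study period", and "The aim will be to end up with 400 (or more) participants at Time 3". So 400 is a completer target and the intake is meant to be larger.

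Appendix 6 holds the agency's material. Its email invitation says "Please note this research project is limited to 900 respondents" and "Once 900 suitable respondents have completed the survey the project will be closed". The screening script in the same appendix lists being out of quota among its screen-out reasons. The quota table that follows, headed "QUOTAS (PER COUNTRY) / ASSIGN TO CELL", gives 25 for each combination of four conditions, two age bands and two genders. The same 25s appear in Table 2 of section 3.1, where they are described as target numbers.

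Section 11.3 bases its power statements on 100 subjects per group and 200 per factor level.

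**The concern.** There are two separate problems, and both bear on how many subjects reach Time 3.

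1. **The rate and the result in section 6.2 do not match.** A loss of two thirds at each step is far heavier than a fall from 900 to 400. Either the rate or the recruitment number is misstated.
2. **The screener carries completer targets where entry quotas belong.** A script that rejects out-of-quota respondents against a grid totalling 400 cannot also admit 900. Agency staff working from Appendix 6 have two stopping points and no rule for choosing between them.

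The analysis needs 100 completers per cell. If the pessimistic rate were real, or if the grid were applied at entry, the trial would end well short of that, and the shortfall would become visible only as follow-up came in.

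**Working it through.** **Inputs.** Three assessment points, hence two transitions (6.2). Drop-out d = 2/3 per transition as written (6.2). Intake 900 and completers 400 (6.2; 900 also in the Appendix 6 invitation; 400 also in 4.1). Quota grid 4 × 2 × 2 cells of 25 (Appendix 6).

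**Step 1: reproduce the 400.** Completers = N × (1 − d)².

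- As written, d = 2/3: 900 × (1/3)² = 100, by way of 300 at Time 2. Reaching 400 would take 400 ÷ (1/3)² = 3,600 recruits.
- As retention, d = 1/3: 900 × (2/3)² = 400, by way of 600 at Time 2. This matches exactly.

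Other ways of using a 2/3 loss do not rescue the sentence. A single loss over the whole study leaves 900 ÷ 3 = 300 (1,200 recruits needed for 400). Inflating 400 by (1 + 2/3) gives 667, and inflating it twice gives 1,111. None of these pairs 900 with 400.

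**Step 2: total the quota grid.** 4 conditions × 2 age bands × 2 genders × 25 = 400, which is 500 short of 900.

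**Step 3: consequence if the grid were an entry cap.** Assume it is enforced at Time 1 and nobody is replaced.

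| Entered | Rate per transition | Time 2 | Time 3 total | Per arm |
|---|---|---|---|---|
| 900 | 2/3 retained | 600 | 400 | 100 |
| 900 | 2/3 lost | 300 | 100 | 25 |
| 400 | 2/3 retained | 267 | 178 | about 44 |
| 400 | 2/3 lost | 133 | 44 | about 11 |

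Each rate gives its own pair: 400 and 178 under retention, 100 and 44 under the literal wording. Figures from different pairs should not be set side by side as if they shared one assumption.

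**Step 4: effect on power.** This uses the pooled two-proportion formula (two-sided 0.05) with the contrasts in section 11.3: 10% against 18% between factor levels, and 10% against 22% between cells.

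| Completers | Factor contrast | Cell contrast |
|---|---|---|
| 400 | 64% | 64% |
| 178 | 34% | 34% |
| 100 | 21% | 21% |
| 44 | 11% | 11% |

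The first row falls below the 80% that section 11.3 states. That is a separate matter. For this point the comparison is of each lower row with 64%.

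**The case against.** **The numbers that drive recruitment are consistent.** 900 and 400 agree to the unit under two-thirds retention, and 900 is repeated in the invitation. On that view one word in section 6.2 is wrong and neither intake nor power changes. This largely stands: an exact match is unlikely to be chance. It does not remove the need to check, because the protocol attributes the rate to an outside agency and nothing in the document shows which share the agency meant.

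**A reader might infer that the trial as planned will finish with 100 subjects, or with 178.** The document supports neither as a forecast. The 100 requires the agency to have meant a two-thirds loss. The 178 requires the grid to be enforced at entry, two-thirds retention, and no replacement. No text says that intake closes at 400; the invitation in the same appendix closes at 900, and section 4.1 plans to over-recruit. The script is marked as a draft and has other features that do not fit this trial: quotas per country in a UK-only study, and a switch between two cells in a four-arm design. The grid may simply be Table 2 copied across.

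**Replacement could fill the gap.** Section 6.1 replaces subjects who withdraw, and section 9.4 replaces incomplete data. Filling each cell to 25 with replacements is one way to reconcile the grid with 400 completers. That makes the 178 conditional. It does not settle the conflict, because no number or timing is given for replacements and section 6.2 deals with attrition by recruiting more at the start.

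**Conclusion.** The point holds in two parts.

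- **Section 6.2 is wrong as written.** Its rate implies 100 completers and its stated result is 400. The most likely explanation is that the retained share was written as the share lost, so that 900 is correct.
- **Appendix 6 contradicts itself and section 6.2.** A grid of 400 with an out-of-quota rejection cannot operate at entry together with a 900-respondent intake. This conflict does not depend on which drop-out rate is right.

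The size depends on how the two are resolved. With 1/3 drop-out and an intake of 900, nothing is lost. With the grid enforced at Time 1 and no replacement, completers fall to about 178 in total (about 44 per arm) at two-thirds retention, or about 44 in total (about 11 per arm) at a literal two-thirds loss. With an intake of 900 and a true two-thirds loss, 100 would complete (25 per arm). It should be put right before launch: it is probably a slip in section 6.2, but the quota conflict sits in the script the agency is meant to run.

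**What to change.** 1. **Section 6.2.** Confirm the rate with the agency. If two thirds are retained, write it as one-third drop-out (two-thirds retained) per phase, with the sequence 900, 600, 400.
2. **Appendix 6, quota table.** Label the 25-per-cell figures as Time 3 completer targets.
3. **Appendix 6, screening quotas.** Set Time 1 quotas by age band and gender that sum to 900, for example 900 ÷ 4 = 225 per stratum. Each stratum would then yield 225 × (2/3)² = 100 completers, or 25 per arm with balanced allocation. This assumes similar retention across strata, which the protocol does not report; if the agency expects otherwise, the split should be uneven. Leave out the arm dimension, because sections 1.4 and 5.1 place allocation at Time 2.
4. **If the agency confirms a two-thirds loss,** restate the expected completers as 100 and revise the power statements in section 11.3, or revisit the intake.

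Steps 1 to 3 cost one query to the agency, one corrected sentence and a revised quota table. They add no subjects beyond the 900 already planned. Step 4 would be a substantive change, which is the reason to ask before launch.
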